### Sample size

As per clinical guidelines, any women and people with a cervix who have not screened under the new HPV screening program will be considered under screened (at least four years overdue); this equates to about 50% or more of eligible screen eligible clients at the services. The baseline screening rate assumption is that 5–10% of screen eligible women and people with a cervix currently move from under screened to screened per 12 months; assuming an increase with policy change to open access to self-collection in 2022 (prior to study intervention) to 20% per 12-month period. To detect a doubling in participation among under screened women and people with a cervix, from 20% in 12 months at baseline to 40%, with 80% power (2-alpha = 5%) and a conventional non-clustered design, would require 91 women and people with a cervix per arm. Allowing up to 12 clusters before and after, and assuming a conservative Intraclass correlation coefficient (ICC) of 0.1, then an average of 50 women and people with a cervix per cluster per period would give a design effect of 5.9, so a total of 1074 women and people with a cervix are required, rounding up to 1200 women and people with a cervix (600 before period, 600 after period). This is feasible given the typical service populations of ACCHOs and the chosen jurisdictions.

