## Materials and methods

*Screen Your Way* will use a before-and-after study design to evaluate the effectiveness of strategies on cervical screening participation among under-screened Aboriginal and Torres Strait Islander women and people with a cervix during the study period. This protocol has been developed following the Standard Protocol Items: Recommendations for Interventional Trials (SPIRIT) checklist (see Fig 1 and Supplementary Information) [31].

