### Analysis

Primary and secondary outcomes will be calculated comparing data from the before (*T0*) and after (*T1*) period. Retention of effects will be measured for services who provide data at 3- and 6-month intervals in the post-implementation period. For the primary outcome, the number and proportion of all screen eligible clients at the services who are under-screened or never-screened at *T1* compared to *T0* (number of under- and never-screened screen eligible clients/number of screen eligible women). Secondary outcomes are cervical screening participation rate (number with a recorded cervical screen in the previous 5-years/number of screen eligible clients), and the number and rate of cervical screens conducted using self-collection (number of tests conducted using self-collection/number of screening tests), and the HPV positivity (number of HPV positive tests/number of screening tests). Descriptive analysis will be used to analyse cervical screening data, with regular interim reports made available to participating services. Primary and secondary outcomes will be calculated comparing data from the before (T0, > 24 months) and after (T1, 12 months) period. The before and after intervention periods will be compared descriptively, and using multi-level logistic regression models clustered on site and allowing for participants who are active in both periods. Due to the small number of participating services, modelled findings and secondary subgroup analyses will be interpreted cautiously, with emphasis on direction and magnitude. A subgroup analysis will also be conducted of the primary outcome among women who have never screened or screened >10 years ago. These will be considered exploratory with no adjustment for multiplicity planned given the implementation focus. Data will be analysed using Microsoft Excel (Microsoft Corporation) and STATA software (StataCorp, version 18).

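### The 80% power is calculated for 12-month conversion among under-screened clients and does not carry over to the primary outcome, the under- or never-screened share of all eligible clients

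*Protocol article*

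**What the plan says.** The Sample size section starts from the rate at which clients "currently move from under screened to screened per 12 months": 5–10% historically, assumed to have risen to 20% after the 2022 policy change. The target is then set: "To detect a doubling in participation among under screened women and people with a cervix, from 20% in 12 months at baseline to 40" per cent. The calculation follows in four steps:

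- size before clustering: "with 80% power (2-alpha = 5%) and a conventional non-clustered design, would require 91 women and people with a cervix per arm";
- number of services: "Allowing up to 12 clusters before and after";
- similarity within services: "assuming a conservative Intraclass correlation coefficient (ICC) of 0.1";
- resulting inflation: "an average of 50 women and people with a cervix per cluster per period would give a design effect of 5.9", which leads to 1074 in all, rounded up to 1200 (600 per period).

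The same section puts the under-screened share at about half of eligible clients or more.

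The Analysis section defines the primary outcome as "the number and proportion of all screen eligible clients at the services who are under-screened or never-screened", with T1 set against T0 and all screen-eligible clients as the denominator. The Cervical screening data section agrees. The secondary outcomes are five-year participation among all eligible clients, the self-collection share of tests, and HPV positivity. The Materials and methods section gives the design's purpose as "to evaluate the effectiveness of strategies on cervical screening participation among under-screened Aboriginal and Torres Strait Islander women", a group it extends to everyone with a cervix.

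**The concern.** The powered quantity is a flow: of those under-screened, how many are screened within 12 months. The primary outcome is a stock: of all eligible clients, how many are under- or never-screened at a time point. They differ in denominator, in type and in effect size. The stock also depends on clients who become newly overdue during the year, which the calculation does not consider. The article gives no expected T0 or T1 prevalence, no detectable difference and no power on the prevalence scale.

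At stake is how the result will be read. The services could double conversion in the target group while the primary outcome moves by a much smaller amount. An inconclusive prevalence result would then be judged against an 80% power figure that was never worked out for it.

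**Working it through.** **1. The plan's own figure.** For 20% versus 40%, two-sided 5%, 80% power, the usual two-proportion formula gives 81.2 per arm, or 90.9 with continuity correction, so 91. Design effect = 1 + (50 − 1) × 0.1 = 5.9. Total = 2 × 91 × 5.9 = 1073.8, so 1074. All three figures reproduce. At 600 per period the effective size is 600 / 5.9 = 101.7, and power for 20% versus 40% is about 88% (uncorrected).

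**2. Translation to the primary outcome.** Take 50% under-screened at T0 (Sample size section) and read 20% and 40% as shares of under-screened clients.

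- Effect of doubling conversion: 0.50 × (0.40 − 0.20) = 0.10, i.e. 10 points of prevalence.
- If newly overdue clients offset the 20% background conversion (0.50 × 0.20 = 10 points), prevalence would stay at 50% without the strategies. T1 is then 0.50 − 0.50 × 0.40 + 0.10 = 40%, so the contrast is 50% versus 40%.
- If nobody becomes newly overdue, T1 = 0.50 × 0.60 = 30%, so the contrast is 50% versus 30%. Ten of those 20 points are the background conversion that the plan assumes anyway.

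Both inflow cases are assumptions; the article gives no inflow figure.

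**3. Power by the plan's method (periods treated as independent).** Power = Φ{[d√n − 1.96√(2p̄(1 − p̄))] / √(p0(1 − p0) + p1(1 − p1))}, with n = 101.7 and no continuity correction.

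- 50% versus 40%: (0.1 × 10.08 − 1.96 × 0.7036) / 0.7 = −0.53, so power is about 30%. For 80% power, 388 per period would be needed before clustering.
- 50% versus 30%: (0.2 × 10.08 − 1.96 × 0.6928) / 0.678 = 0.97, so power is about 83%. For 80% power, 93 per period would be needed before clustering.
- With 58% under-screened at T0 (assumed from the 42% screened figure in the Introduction), the matching contrasts, 58% versus 46.4% and 58% versus 34.8%, give about 38% and 92%.

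**4. Allowing for the same services in both periods.** If site effects correlate r between periods, the design effect for the before–after difference is 1 + (m − 1) × ICC − m × ICC × r. The article states no r, so a range is shown for 50% versus 40%, 12 services, ICC 0.1. The last column uses the 120 or more active clients per service required in Step 1.

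| Assumed r | Design effect, m = 50 | Effective n | Power, m = 50 | Power, m = 120 |
|---|---|---|---|---|
| 0 | 5.9 | 101.7 | 30% | 32% |
| 0.5 | 3.4 | 176.5 | 47% | 54% |
| 0.8 | 1.9 | 315.8 | 72% | 85% |
| 0.9 | 1.4 | 428.6 | 84% | 96% |

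Clients present in both periods are not credited here. The number of services also matters. Step 1 sets a minimum of six, while the calculation allows up to 12. With six services of 50, the same formula gives 17% at r = 0 and 55% at r = 0.9.

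**The case against.** The strongest reply is that low power does not follow from the mismatch, and that stands. A reader might infer that the study has only about 30% power, or that 12 services at ICC 0.1 can never do better than about 30–34% however many clients they contribute. The documents do not support either inference. Both require site effects to be uncorrelated between periods. Yet the same services are measured twice, and the Analysis section plans multilevel models that cluster on site and allow for clients active in both periods. Keeping 50 per service also understates the data for an outcome whose denominator is all eligible clients.

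Three further points are fair:

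- The 10-point shift rests on one reading. The Sample size section first ties the base rate to screen-eligible clients and only then refers to under-screened clients. If 20% and 40% were shares of all eligible clients, the shift would be 20 points.
- The protocol says modelled findings will be interpreted cautiously, and judges success by movement towards 70% participation and, equally, by participants' own definitions. This softens the consequence, but does not withdraw the 80% figure.
- A reader might conclude that conversion should replace prevalence as the primary outcome. That would change the primary outcome during implementation in a retrospectively registered study. It would also depend on rebuilding a pre-implementation cohort that the article does not describe, from records it calls incomplete.

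**Conclusion.** The point holds as a mismatch of endpoints, not as an arithmetic error. The 80% power belongs to a 12-month conversion contrast that is not among the listed outcomes, and the article gives no power for the outcome it calls primary.

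Its size is uncertain, because the article does not state the inputs. With 50% under-screened at T0 and rates read as shares of under-screened clients, power at 12 × 50 runs from about 30% to 84% for 50% versus 40% as the assumed between-period correlation goes from 0 to 0.9. It is about 83% for 50% versus 30% even at zero correlation. The low figures are one end of that range. The documents support saying that 80% has not been shown for the primary outcome; they do not support saying that power must fall below it.

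**What to change.** Replace the sample-size paragraph with the power or precision for the prevalence outcome in the Analysis section. State:

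- the expected T0 prevalence;
- the expected T1 prevalence, including the inflow of newly overdue clients;
- whether 20% and 40% are shares of under-screened or of all eligible clients;
- cluster size as all eligible clients per service;
- the number of services actually recruited;
- an assumed between-period correlation of site effects, with a range.

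Withdraw the 80% claim for the primary outcome unless this calculation meets it.

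Where dated client-level records allow, add a secondary outcome: among clients under- or never-screened at the start of a 12-month window, the proportion screened within it, comparing equal pre-implementation and implementation windows. The existing calculation would then apply to a listed outcome. Equal windows need stating, because the Analysis section now sets a before period of more than 24 months against 12 months after.

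The cost is a wording change before final analysis and a little more analysis work; no extra clients are needed. The restated power may look less favourable than 80%.

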### Limitations

The study uses cervical screening data from available sources, including practice management software. This presents several limitations as screening records within these platforms can contain inconsistencies and incomplete fields. To mitigate this, strategies focusing on data audits and cleaning will be prioritised (where feasible). Where this is not possible, we will explicitly acknowledge the resulting uncertainty. Missingness will be assessed descriptively to characterise data quality, but no formal imputation will be undertaken consistent with the study’s implementation focus.

### Yarns

Semi-structured Yarns and Yarning circles will be used to explore providers’ and clients’ views and experiences of the project, evaluate implementation strategies and to provide contextual information to support cervical screening participation data. Data collection will include individual and group Yarns with approximately 20–30 service staff involved in cervical screening strategies (including doctors, nurses, and Aboriginal Health Practitioners) and separately with 20–40 women and people with a cervix who are clients of the service and who were offered cervical screening. All participants (both screening participants and providers) will provide individual informed consent prior to the Yarns or Yarning circles. Yarns may take place any time during the implementation (after) period of the study but will be concentrated towards the end of, or after, the 12 months allocated to the implementation of strategies. Yarns may take place in-person, online via virtual meeting software or over the phone and will be audio-recorded and transcribed verbatim.

Yarning is a culturally appropriate Indigenous research methodology grounded in Aboriginal and Torres Strait Islander peoples’ traditional ways of communicating, building relationships and sharing knowledge [45,46]. It involves distinct but interconnected types of Yarning including social Yarning to establish relationality and trust, research Yarning to explore the research topic, and therapeutic Yarning to create space for healing conversations if needed [45]. Where possible, trained female Aboriginal and/or Torres Strait Islander researchers will Yarn with participants. Non-Indigenous researchers may also conduct Yarns with appropriate training and mentoring from Aboriginal and Torres Strait Islander people to ensure a culturally safe approach.

Data (transcripts and field notes) will be managed with NVivo software (QSR International, V.12). Framework analysis (also known as “codebook thematic analysis” [47]) will be used to systematically identify themes in the data, using both inductive and deductive coding [48]. An initial coding framework will be developed by Aboriginal and Torres Strait Islander researchers, drawing on the Indigenist research approach, the Lowitja Evaluation Framework, and early inductive coding of a subset of transcripts. This framework will be refined throughout the study to recognise and respect the sovereignty, knowledge systems, and diverse contexts of each participating service and the community they serve. In line with the Indigenist research approach, Aboriginal and Torres Strait Islander people will lead analysis, with support from non-Indigenous researchers. This approach centres Aboriginal and Torres Strait Islander people’s worldviews and lived experiences in the interpretation and analysis of the data. The Lowitja Evaluation Framework will guide analysis, ensuring social, structural and environmental factors influencing the uptake of self-collection are considered alongside individual level factors and grounded within an Indigenist research approach.

### Process data

Process data will be used to examine the fidelity of strategy implementation and explore factors that may have influenced their effectiveness in increasing cervical screening participation. Process data will include service level information including the service size, number of eligible clients, the number of cervical screening providers and provider type, remoteness; as well as information on the range of activities implemented in the models (e.g., resources/materials used, provider training activities, community events undertaken, location of self-collect, recalls set, reports provided). Any unrelated activities that may have influenced health care attendance (e.g., major cultural or other health promotion activities) will be captured. A worksheet based on the Framework for Reporting Adaptations and Modifications to Evidence-based Implementation Strategies (FRAME-IS) [49] will be used to collect process data. This tool will allow the research team and the ACCHOs to track when, why and how strategies have been implemented and any associated costs or time.

## Discussion

### Dissemination plan

Our co-design process will develop materials, procedures and processes which can be used broadly, beyond the research. Our partnership and governance structure will ensure efficient knowledge transfer mechanisms, facilitated through respectful collaboration, including leaders in the Aboriginal community-controlled sector, cervical screening and academia. Findings will be disseminated to support the evidence-informed national scale up of self-collection. This will include publication in peer review journals and presentations at conferences. Publications will adhere to CONSolIDated critERtia for strengthening the reporting of health research involving Indigenous Peoples (CONSIDER) statement [50]. Findings will also be shared in a variety of other formats previously shown to be successful in translating implementation research findings into policy and practice including translational workshops, evidence briefs and presentations, reports and the creation of resources.

### Implications

This research directly aligns to recommendations in Australia’s National Strategy for the Elimination of Cervical Cancer [51] and the World Health Organization’s Global Strategy to Accelerate the Elimination of Cervical Cancer [2] where the immediate priority is: to save women’s lives in the short term by scaling up screening participation and receipt of treatment globally by 2030. Overcoming universal self-collection implementation issues will be necessary to increase participation and achieve equity in cervical cancer elimination for Aboriginal and Torres Strait Islander people.

Co-designed strategies have the potential to transform practice and outcomes, and study findings will be readily transferrable to ACCHOs across Australia. With change, they are also likely to be adaptable to Indigenous women and people with a cervix in other countries. By encouraging community-driven innovations relating to self-collection, we aim to embed these practices in ACCHO service delivery long after the study is completed and provide a way to take the findings and implement nationally. This will both honour community voices and maximize cervical screening participation through a mechanism that we know works. This is critical to ensure that Aboriginal and Torres Strait Islander women and people with a cervix are not left behind as Australia approaches elimination of cervical cancer.

## Abbreviations

ACCHO: Aboriginal Community Controlled Health Organisation
AIATSIS: Australian Institute of Aboriginal and Torres Strait Islander Studies
AHMRC: Aboriginal Health and Medical Research Council of NSW
AMSANT: Aboriginal Medical Services Alliance Northern Territory
HPV: Human Papillomavirus
NACCHO: National Aboriginal Community Controlled Health Organisation
NCSP: Australia’s National Cervical Screening Program
NCSR: National Cervical Screening Register
NSW: New South Wales
NT: Northern Territory
QAIHC: Queensland Aboriginal and Islander Health Council
Qld: Queensland
